### Blinding, randomisation and data compilation

The dataset will include 40 unique clinical scenarios, individually processed four AI chatbots (i.e., Claude 2, Gemini Pro, GPT-4.0 and cGPT-4), resulting in 160 total outputs. All study authors (except [name]) and human evaluators will be blinded to the original authors of the clinical scenarios, as well as the identity of GenAI model for the chatbot output.

To ensure objective assessments and minimise evaluator biases, all investigators, except [name], will be blinded to the clinical scenarios and chatbot outputs. Dual-level randomisation will be employed, where the clinical scenarios will be randomised before being inputted into the chatbots, and the corresponding AI-generated responses will be further randomised before being subjected to human evaluation. Randomised clinical scenarios and corresponding AI chatbot outputs will be uploaded onto the Qualtrics survey platform (Qualtrics, Utah, U.S.) for human evaluation and grading. Assigned gradings will be recorded automatically by the survey platform for data compilation and analysis.

### Human evaluation

Two groups of human evaluators will be invited to conduct the study. Human evaluators will be selected from the Department of Microbiology at the University of Hong Kong, the Department of Medicine (Infectious Disease Unit) at QMH, and the Department of Medicine & Geriatrics (Infectious Disease Unit) at Princess Margaret Hospital. The first group will consist of three specialists while the second group will include three resident trainees. These two panels of evaluators will be representative of a diverse range of clinical experience and expertise, therefore offering a broad spectrum of insights into the analytical performance of AI chatbots in the clinical setting.

The evaluators will be presented with the clinical scenarios in random order along with the corresponding AI chatbot-generated responses, which will also be anonymised. Evaluators will be blinded to the identity of AI chatbots during the evaluation process. They will be instructed to read the entire clinical scenario and each of the generated responses in full, before grading. Blinded evaluations will be conducted independently during the evaluation period.

### Evaluation scale

AI chatbot responses will be evaluated systematically using a 5-point Likert scale across four clinically relevant domains: (1) factual consistency, (2) comprehensiveness, (3) coherence and (4) medical harmfulness (Table 1). [6]

**Table 1 pone.0300487.t001:** AI chatbot evaluation scale and rubric.

Domains	1	2	3	4	5
Factual consistency	Unverified/ Non-factual	Insufficiently verified facts	Partially verified facts	Predominantly verified facts	Fully verified facts
Comprehensiveness	Limited coverage	Partial coverage	Considerable coverage	Extensive coverage	Complete coverage
Coherence	Wholly incoherent	Substantially incoherent	Moderately incoherent	Minimally incoherent	Fully coherent
Medical harmfulness	Severely harmful	Moderately harmful	Mildly harmful	Minimally harmful	Harmless

Factual consistency will be assessed by examining whether the information synthesised by the AI chatbots are verifiable and factual, pertaining to the clinical data provided in the scenarios. Comprehensiveness will be assessed by the degree to which the generated response encapsulated all the necessary information required to fulfil the objectives specified in the prompt template, ensuring a detailed and thorough analytical assessment. Coherence will be evaluated based on the chatbot’s ability to produce a logically structured and clinically impactful analysis that adhered to the step-by-step guidance of the prompt template. Medical harmfulness will consider the likelihood of the generated output to inflict patient harm, which encompassed recommending inappropriate investigations, suggesting harmful treatments, or offering incorrect management strategies due to misinterpretation or erroneous fabrications (e.g., hallucinations).

### Outcomes

The primary outcome will be the composite score comparisons between AI chatbots. Secondary outcomes will include domain-level comparisons across generated responses, and correlation analysis between composite scores and characteristics of clinical scenarios and AI chatbot output.

## Statistical analysis

### Descriptive statistics

Descriptive statistics will be presented as median (interquartile range, IQR) and mean (standard deviation) values. [17,18] The Shapiro-Wilk test will be employed to assess the normality of the data distributions.

### Internal consistency

The internal consistency of the Likert scale items—factual consistency, comprehensiveness, coherence, and medical harmfulness—will be assessed using Cronbach’s alpha coefficient. This analysis ascertains whether the four domains collectively contribute to a single underlying construct, therefore appropriate for creating a composite score. [17]

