## Materials and methods

This project aims to evaluate the potential role of AI chatbots to assist clinicians by providing immediate analysis and suggestions to enhance and augment clinical practice and workflow. The protocol employs a universal standardised prompt template to compare between AI chatbot responses against real-life clinical scenarios. Generated responses will be evaluated by a panel of practicing clinicians [specialists (n =  3); resident trainees (n =  3)] using a 5-point Likert scale. [6] Human evaluators will serve as domain experts with specific knowledge in clinical microbiology and virology, as well as internal medicine and clinical infectious diseases (Fig 1).

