### Composite score evaluation

Composite scores (range, 4-20) will be constructed by the summation of the mean scores of all four domains. Differences in mean composite scores among chatbots will be examined using one-way Analysis of Variance (ANOVA). Tukey’s Honest Significant Difference (HSD) test will be applied for post-hoc pairwise comparisons. [18,19] Paired t-tests will be used for within-group comparisons of composite scores between specialist and non-specialist evaluators.

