Additionally, our protocol will rely on historical clinical data, which will not capture and reflect the dynamic and often unpredictable nature of real-time clinical decision-making. The inherent variability and fluidity of real-life clinical environments are difficult to replicate in a cross-sectional observational study, invariably limiting the generalisability of our findings.

The integrity of chatbot-generated responses is directly tied to the quality of inputted clinical data. [24] Inaccuracies, inconsistencies, or gaps in the original clinical documents may significantly compromise the performance of GenAI models and mask their true capabilities. Advances in natural language processing to automatically extract clinical data from electronic health records may help to mitigate some of these data quality challenges by providing more comprehensive inputs. [25]

Limited number of human evaluators represent another limitation. The study outcomes are dependent on the evaluators’ proficiency and their interpretation of the generated responses. Selected evaluators’ perspectives may not encapsulate the wide-ranging opinions and approaches that exist within the broader medical community, potentially leading to evaluations that do not fully capture the diversity of clinical judgments.

Finally, there are concerns regarding the evaluation scale utilised in this study, which has not been validated and may introduce subjective biases in the evaluation process.

To conclude, this study will represent a significant step towards understanding the analytical potentials of AI chatbots in the clinical setting. While the initial results will provide valuable insights into the capabilities and limitations of AI chatbots in processing and analysing clinical data in a structured manner, the limitations identified must be carefully considered.

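### Cronbach's alpha assumes that the four domains form one construct and cannot test it, so it does not justify the primary composite; it can exceed 0.70 with harm unrelated to the rest

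*Protocol article*

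**What the plan says.** The Internal consistency section (under Statistical analysis) states that the internal consistency of the four domains "will be assessed using Cronbach’s alpha coefficient", and then says what the result will establish: "This analysis ascertains whether the four domains collectively contribute to a single underlying construct, therefore appropriate for creating a composite score". This is the only justification that the article gives for adding the domains together.

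The sum matters because of its role. The Outcomes section says: "The primary outcome will be the composite score comparisons between AI chatbots". The Composite score evaluation section defines it: "Composite scores (range, 4-20) will be constructed by the summation of the mean scores of all four domains". Table 1 scores all four domains with 5 as the best grade, so harm points the same way as the others and needs no reverse scoring.

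Two further statements bear on the point. The Domain-level evaluation section compares the chatbots on each domain separately. The limitations in Results and discussion describe the rating scale as one "which has not been validated and may introduce subjective biases in the evaluation process".

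**The concern.** Alpha is a summary of average covariance among items. Read as reliability, it takes a single dimension as given; it does not ask whether there is one. The article turns this round and treats alpha as the evidence for a single construct.

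What is at stake is whether harm belongs in the primary sum. On the Table 1 scoring, an output graded 1 for harm (the worst grade) and 5 on the other three domains totals 1 + 15 = 16. An output graded 4 throughout also totals 4 × 4 = 16. Treating the two as equal is easier to defend if the domains move together, and alpha is the check offered for that. If the check can pass when they do not, the report could call the composite one construct without having shown it.

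**Working it through.** **Figures in the article.** Four domains graded 1 to 5 give a sum from 4 × 1 = 4 to 4 × 5 = 20, which reproduces the stated range. The 40 scenarios and four chatbots give 40 × 4 = 160 outputs, as stated. There are six evaluators (three specialists, three trainees). The article states no alpha value, cut-off, inter-domain correlation or SD, so everything below on those is assumed and shown as a range.

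**Step 1: can alpha tell structures apart?** For k = 4 items with equal SDs and mean inter-item correlation m, alpha = 4m/(1 + 3m). There are six pairs of items.

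- One common factor, all six correlations 0.40: m = 0.40.
- Three domains at 0.8 with each other, harm at 0 with each: m = (3 × 0.8 + 3 × 0)/6 = 0.40.
- Two separate pairs, 0.8 within and 0.2 between: m = (2 × 0.8 + 4 × 0.2)/6 = 0.40.

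In all three, alpha = 1.6/2.2 = 0.727. This needs no cut-off.

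**Step 2: harm unrelated, equal SDs.** If the other three domains share a correlation r, then m = 3r/6 = r/2 and alpha = 2r/(1 + 1.5r).

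| r among the other three | alpha |
|---|---|
| 0.5 | 1.0/1.75 = 0.57 |
| 0.6 | 1.2/1.90 = 0.63 |
| 0.7 | 1.4/2.05 = 0.68 |
| 0.75 | 1.5/2.125 = 0.71 |
| 0.8 | 1.6/2.20 = 0.73 |
| 0.9 | 1.8/2.35 = 0.77 |
| 1.0 | 2.0/2.50 = 0.80 |

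Alpha reaches 0.70 when 2r = 0.70 + 1.05r, that is r = 0.70/0.95 = 0.737.

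**Step 3: unequal SDs.** Let the harm SD be s times that of the others. Then alpha = 8r/(3 + 6r + s²), and the r needed for 0.70 is 0.7(3 + s²)/3.8. This gives 0.60 at s = 0.5, 0.66 at s = 0.75, 0.74 at s = 1, 0.84 at s = 1.25 and 0.97 at s = 1.5. A harm item that varies little is the easiest to miss.

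**Step 4: do the proposed checks separate the structures in Step 1?** Three-item alpha is 3m/(1 + 2m).

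- Dropping harm from the second structure raises alpha from 0.73 to 2.4/2.6 = 0.92, a clear signal. In the one-factor structure, dropping any item lowers it to 1.2/1.8 = 0.67.
- In the two-pair structure, dropping any item leaves correlations of 0.8, 0.2 and 0.2, mean 0.40, so alpha is again 0.67. Item-dropping does not reveal this structure, but the correlation matrix does at once.
- A one-factor model fits the second structure with a harm loading of zero, so the loading must be read as well as the fit. It fails on the two pairs, because the products of opposite correlations differ (0.8 × 0.8 = 0.64 against 0.2 × 0.2 = 0.04).

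The three checks are therefore complementary.

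**Step 5: alpha and rater agreement.** Ratings were simulated for 160 outputs, six raters and four domains. Each rater had a private overall impression of each output (variance 0.75) plus item noise (variance 0.25), with nothing shared between raters. Alpha over the individual ratings was 0.89, while the one-way ICC of the composite was -0.01. This is a deliberate extreme. It shows only that alpha across domains and agreement across raters are different quantities.

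**The case against.** **Alpha may well flag an unrelated harm item.** This stands. At r = 0.5-0.7 with equal SDs it would fall below 0.70, and with a widely varying harm item it would do so for nearly any r. A reader might infer that alpha stays above 0.70 whenever harm is unrelated. The arithmetic does not support that, and the cut-off is not the article's.

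**Zero correlation is a constructed case.** Also fair. Table 1 and its explanation count mistaken management arising from fabricated content as harm, which overlaps with factual consistency. Nothing in the article makes full independence likely. The case shows what alpha cannot detect; it does not predict the data.

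**Harm is already looked at separately.** True. Domain-level comparisons are secondary outcomes and are run for each domain, whatever alpha shows. A reader might infer that the plan hides safety inside the sum; it does not. But a secondary harm comparison does not make the statement about the primary composite correct.

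**The primary test does not depend on alpha.** Correct: the ANOVA and Tukey results are the same whatever alpha turns out to be. No bias, error rate or changed ranking has been shown. What changes is what may be said about the quantity being compared.

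**Rater agreement may be covered elsewhere.** A reader might infer that agreement among the six evaluators will never be assessed. The article names no agreement statistic, and its specialist versus non-specialist paired t-test compares means. But an article condenses the plan, and a full analysis plan could include one. The silence is not counted as an error here.

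**Conclusion.** The sentence in the Internal consistency section is wrong as written, and a fuller analysis plan could not make it right: alpha assumes one dimension and cannot ascertain it. Since that sentence is the only stated ground for the primary composite, it should be corrected.

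The size is conditional. An unrelated harm domain would pass a 0.70 cut-off only if the other three correlate at about 0.74 or more with equal SDs, or from about 0.60 to 0.97 as the harm SD goes from half to 1.5 times that of the others. With equal SDs, alpha cannot exceed 0.80 in that case. These figures rest on assumed correlations, SDs and cut-off. The point that one alpha value fits several structures rests on none of them.

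The finding concerns what the composite may be claimed to measure. It does not show that the chatbot comparison is invalid. That a high alpha would not demonstrate rater agreement is a secondary caution.

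**What to change.** 1. Replace the claim in the Internal consistency section with a statement that alpha describes the internal consistency of the four domain scores and is not taken as evidence that they measure one construct.
2. Rest the case for the composite on three results at output level: the 4 × 4 inter-domain correlation matrix, alpha with each domain dropped in turn, and a one-factor check in which both the fit and the harm loading are reported.
3. If harm does not fit, repeat the primary comparison with a three-domain composite as a sensitivity analysis, and present it next to the separate harm comparison already planned under Domain-level evaluation. What counts as not fitting should be written down before the chatbot comparisons are seen.
4. Optionally, report an ICC across the six evaluators from the same ratings, unless the full analysis plan already provides for it.

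The four-domain composite stays primary and no new data are needed. The cost is a little extra analysis and, possibly, a less favourable description of the composite.

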### Composite score evaluation

Composite scores (range, 4-20) will be constructed by the summation of the mean scores of all four domains. Differences in mean composite scores among chatbots will be examined using one-way Analysis of Variance (ANOVA). Tukey’s Honest Significant Difference (HSD) test will be applied for post-hoc pairwise comparisons. [18,19] Paired t-tests will be used for within-group comparisons of composite scores between specialist and non-specialist evaluators.

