### AI chatbots

AI chatbots will be accessed via Poe (Quora, California, U.S.), a third-party subscription-based AI software platform. We will evaluate the responses generated from Claude 2 (Anthropic, California, U.S.), Gemini Pro (Google DeepMind, London, U.K.), GPT-4.0 (OpenAI, California, U.S.), and a custom bot based on GPT-4.0 (cGPT-4).

The custom bot will be created through the “Create bot” function within the Poe interface. GPT-4 is selected as the foundation model for the custom bot. Four widely recognised clinical references will be integrated into the knowledge base of the custom bot, which will include: Török, E., Moran, E. and Cooke, F. (2017) *Oxford Handbook of Infectious Diseases and Microbiology*. Oxford University Press. [12]; Mitchell, R.N., Kumar, V., Abbas A.K. and Aster, J.C. (2016). *Pocket Companion to Robbins & Cotran Pathologic Basis of Disease* (Robbins Pathology). Elsevier. [13]; Sabatine, M.S. (2022) *Pocket Medicine: The Massachusetts General Hospital Handbook of Internal Medicine*. Lippincott Williams & Wilkins. [14] and Gilbert, D.N., Chambers, H.F., Saag, M.S., Pavia, A.T. and Boucher, H.W. (editors) (2022) *The Sanford Guide to Antimicrobial Therapy 2022*. Antimicrobial Therapy, Incorporated. [15] These references aim to provide domain-specific knowledge to inform the generated responses by the custom bot.

The AI chatbot response variability is configured to the pre-determined temperature setting as defined by Poe, which will be most applicable to the general user. Temperature, a hyperparameter in the GenAI model, determines the degree of randomness in its responses. A lower setting produces more predictable responses while a higher setting produces answers with greater variability and creativity. [16] The preset temperature configurations for the AI chatbots are as follow: Claude 2 at 0.5, GPT-4 at 0.35, and the custom bot at 0.35; however, the exact temperature setting for Gemini Pro is not publicly available.

Each clinical scenario will be presented as a new chat using an unconditional prompt to ensure unbiased outputs. All scenarios will be inputted by [name] and processed on a pre-specified date to ensure output consistency.

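### One-way ANOVA with Tukey HSD ignores that all four chatbots answer the same 40 scenarios and gives every pair one pooled standard error, which is likely to be most oversized for GPT-4 versus the custom bot

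*Protocol article*

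**What the plan says.** The Outcomes section states: "The primary outcome will be the composite score comparisons between AI chatbots". The Composite score evaluation section assigns this to a one-way ANOVA on mean composite scores and adds that "Tukey’s Honest Significant Difference (HSD) test will be applied for post-hoc pairwise comparisons". It mentions no scenario effect. In the same section, the comparison of specialist with non-specialist evaluators is given paired t-tests, so pairing is recognised there but not for the chatbots.

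The design is fully crossed. Under Blinding, randomisation and data compilation: "The dataset will include 40 unique clinical scenarios, individually processed four AI chatbots", "resulting in 160 total outputs".

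The AI chatbots section describes how the chatbots are related: "GPT-4 is selected as the foundation model for the custom bot". Preset temperatures are "Claude 2 at 0.5, GPT-4 at 0.35, and the custom bot at 0.35", with Gemini Pro's setting not public. Only the custom bot receives the four reference works.

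**The concern.** A hard case tends to lower every chatbot's score and an easy one to raise it. A one-way analysis leaves that shared variation in the error term, although it cancels in any within-scenario difference. With positive within-scenario correlation, the planned standard error is therefore too large for every pair.

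Tukey HSD adds a second layer. It uses one error term for all six pairs, whereas the variance of a paired difference depends on that pair's own correlation. GPT-4 and its derivative, at the same temperature, are the pair most likely to move together, so the common standard error would fit them worst. Adding scenario as a block removes the first problem but not the second, because a blocked ANOVA or random-intercept model still has one common error term.

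At stake is the contrast between GPT-4 with and without the added literature, which the Introduction presents as a feature of the study. A real benefit could be reported as no difference.

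**Working it through.** **The plan's own figure.** 40 scenarios × 4 chatbots = 160 outputs, as stated; 4 × 3 / 2 = 6 pairs. The article gives no SD, correlation, target difference or power, so there is no power figure to reproduce.

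**Assumptions.** One mean composite per output, normal scores, SD 1 for each chatbot, correlation 0.4 for five pairs, correlation ρ for GPT-4 versus custom bot, and a true difference of 0.4 SD.

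**Standard errors for this pair.**
- As planned (one-way): √(2/40) = 0.224, whatever the correlations.
- Scenario-blocked, pooled: √(2(1 − ρ̄)/40), with ρ̄ = (5 × 0.4 + ρ)/6.
- The pair's own: √(2(1 − ρ)/40).

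| ρ | Own SE | Blocked SE | One-way / own | Blocked / own |
|---|---|---|---|---|
| 0.4 | 0.173 | 0.173 | 1.29 | 1.00 |
| 0.6 | 0.141 | 0.168 | 1.58 | 1.19 |
| 0.7 | 0.122 | 0.166 | 1.83 | 1.35 |
| 0.8 | 0.100 | 0.163 | 2.24 | 1.63 |

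**Difference needed for significance.** The Tukey multipliers (studentized range for four means, divided by √2) are 2.597 on 156 df (one-way) and 2.606 on 117 df (blocked). As planned, the observed difference must exceed 2.597 × 0.224 = 0.58 SD. At ρ = 0.7, the blocked Tukey needs 2.606 × 0.166 = 0.43 SD. A paired t-test at the first Holm step (0.05/6, 39 df, multiplier 2.780) needs 2.780 × 0.122 = 0.34 SD.

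**Power for this pair at a true 0.4 SD** (simulation of 40 × 4 normal scores):

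| ρ | One-way Tukey (plan) | Blocked Tukey | Paired t, Holm |
|---|---|---|---|
| 0.4 | 16% | 39% | 36% |
| 0.6 | 11% | 40% | 55% |
| 0.7 | 8% | 40–41% | 70% |
| 0.8 | 5% | 40–42% | 89% |

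A hand check at ρ = 0.7 under the plan: (0.58 − 0.40)/0.122 ≈ 1.48, an upper tail of about 7%, in line with the simulated 8%.

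**Pairs of unrelated models**, with ρ between 0.6 and 0.8: about 16% as planned, 41–45% blocked, 35–37% paired with Holm. If scenarios induce no correlation at all, paired contrasts lose 2–3 points against the plan.

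**Other assumptions** (other pairs at 0.5, difference 0.4 SD; paired test at 0.05/6). The blocked Tukey falls short of the pair-specific test by 4, 18, 34 and 41 points when this pair's correlation exceeds the rest by 0.1, 0.2, 0.3 and 0.4. At equal correlation it is 6–7 points better. With other pairs at 0.5, this pair at 0.8 and a difference of 0.6 SD, power is 58% as planned, 98% blocked and 100% pair-specific.

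**The case against.** The strongest reply is that every power figure depends on three inputs the article does not supply: the general correlation, this pair's correlation and the effect size. That stands. The shared foundation model makes a closer correlation likely, not certain, and the added references could weaken it. A reader might infer that this contrast stays badly under-powered even after blocking. The documents do not support that as a general statement: with other pairs at 0.7 and this pair at 0.8–0.9, a blocked Tukey has 82–91% power at 0.4 SD.

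A reader might also infer from the unequal temperatures, and from the article's remark that "A lower setting produces more predictable responses while a higher setting produces answers with greater variability and creativity", that pooling produces false positives in pairs with a noisier chatbot. That fails for the plan as written. Take SD 2 for one chatbot, 1 for the rest and correlation 0.4. The one-way variance of a difference is 2 × (4 + 1 + 1 + 1)/4 = 3.5, against a true 4 + 1 − 2 × 0.4 × 2 = 3.4, so the standard error is not too small. Simulated family-wise error is about 2%. The 7.0–7.4% found in this setting arises only under a blocked pooled-error analysis, which is not planned. Nor does the article link temperature to the SD of composite scores across different cases.

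The article does not name GPT-4 versus custom bot as a key contrast. Its importance follows from the design: no other pair differs only in the reference works.

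Finally, an article condenses a fuller plan. Covariance detail could sit elsewhere, but the test for the primary outcome is named here, and that test has no place for the scenario.

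**Conclusion.** The point holds as a loss of power, not as an inflation of error. The larger part comes from omitting scenario: at a common correlation of 0.4, blocking alone raises power for a 0.4 SD difference from 16% to 39%. The pooled error term is a second-order problem. It matters for GPT-4 versus custom bot if that pair's correlation exceeds the others' by roughly 0.2 or more and the true difference is modest (about 0.2–0.5 SD). In the main example, pair-specific standard errors then add about 15 to 48 points over a blocked Tukey.

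All sizes assume 40 scenarios, equal SDs, normal scores and one mean composite per output. If the 160 × 6 = 960 individual ratings were analysed instead, dependence within rater would be a further problem.

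**What to change.** In Composite score evaluation, replace the one-way ANOVA and Tukey HSD with the six paired contrasts on scenario-level composite differences, each with its own standard error, Holm-adjusted across the six. An alternative is a scenario-level model with an unstructured 4 × 4 chatbot covariance and max-t adjusted simultaneous 95% confidence intervals. Avoid a compound-symmetric or otherwise pooled error term. State that the unit is one mean composite per output.

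The cost is analysis wording only; no new data are needed. Against a scenario-blocked Tukey, pairs of unrelated models lose about 3 points at equal correlation and somewhat more (41–45% down to 35–37%) when GPT-4 and the custom bot are closer. Part of that gap reflects a blocked standard error that is 3–6% too small for those pairs. Against the plan as written, every pair gains power once scenarios induce moderate correlation.

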### Statistical significance

A p-value of less than 0.05 will be considered statistically significant.

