## Results and discussion

In this protocol, we hypothesise that analytical performance of AI chatbots in real-life clinical scenarios could be objectively measured using a standardised assessment protocol and graded by clinically experienced human evaluators. We also hypothesise that in the evaluation of structured clinical scenarios, AI chatbots primed with domain-specific knowledge in medical sciences could generate clinically relevant recommendations within the boundaries of the prompt template and the scope of the provided clinical data. We further hypothesise that AI chatbots could assist clinicians by providing accurate, comprehensive, and coherent analysis in clinical consultations, without posing medical harm.

In designing this study, we will employ several strategies to limit major biases. Recognising the critical importance of data quality, we will institute a rigorous data curation phase where clinical documents will be reviewed, cleaned, and standardised to ensure AI chatbot operates on high-integrity data. To address the potential for evaluator bias, we will adopt multiple blinding and randomisation procedures, including evaluator blinding, scenario randomisation and response randomisation. Moreover, we will select two diverse groups of evaluators to encompass a broad spectrum of clinical experiences, ensuring our study reflects the varied insights from both specialists and non-specialist doctors.

Nonetheless, there remain several key limitations that bear consideration when interpreting this study. One of the primary limitations is that this study does not accommodate for the inherent potential of continued learning and adaptation by AI chatbots over time. Advances in machine learning suggest that GenAI performances could be improved with continued exposure to clinical scenarios [22], a factor that our current zero-shot prompting protocol does not address. To refine the performance and reliability of LLMs, future research may consider longitudinal study designs or continuous evaluation methods to track the evolution of AI performance with the use of reinforcement learning and human feedback. [23]

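### The paired t-tests of specialist against non-specialist scores leave rater severity out of the error term, so with three raters per panel they cannot support a claim about expertise

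*Protocol article*

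**What the plan says.** Under Composite score evaluation, the article fixes the test: "Paired t-tests will be used for within-group comparisons of composite scores between specialist and non-specialist evaluators". The score is defined in the same section: "Composite scores (range, 4-20) will be constructed by the summation of the mean scores of all four domains". The Statistical significance section sets the threshold: "A p-value of less than 0.05 will be considered statistically significant".

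The panels are described under Human evaluation: "The first group will consist of three specialists while the second group will include three resident trainees". The same section says what they stand for: "These two panels of evaluators will be representative of a diverse range of clinical experience and expertise". The Introduction likewise presents the two tiers as levels of expertise and clinical experience, and the discussion gives the purpose as "ensuring our study reflects the varied insights from both specialists and non-specialist doctors".

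Forty scenarios go through four chatbots, "resulting in 160 total outputs", and the evaluators grade independently: "They will be instructed to read the entire clinical scenario and each of the generated responses in full, before grading".

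The Outcomes section does not list the panel comparison as primary or secondary. The article describes no rater term. Its one reliability measure, Cronbach's alpha under Internal consistency, concerns the four domains and not agreement between raters. Among the limitations, the article concedes that evaluators are few, that results depend on their proficiency and interpretation, and that the scale is unvalidated.

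**The concern.** Expertise varies between raters and not between outputs: each rater is either a specialist or a trainee. The replication that bears on an expertise effect is therefore three raters against three. A paired t-test needs pairs, and six different people in two panels form none. The only workable pairing sets the specialist panel's score against the trainee panel's score on the same output. Outputs then act as the replicates, 40 if within-group means within chatbot or 160 if pooled. The article does not say which.

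The error term then reflects only how much the panel gap varies from output to output. Any steady difference in severity between the individuals who happen to sit on each panel is counted as signal. Grading more outputs makes the test more certain of that difference without saying more about expertise.

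At stake is the reading of the dual-tier design, which the Introduction presents as a distinctive feature and for which this is the only named test. A small p-value could be taken to show that specialists and trainees judge chatbot advice differently when it shows only that these three people differ from those three.

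**Working it through.** **Plan's own figures.** The output count agrees: 40 × 4 = 160. The article gives no power, sample-size or variance figure for this comparison, so there is nothing else to reproduce.

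**Inputs from the article.** Three raters per panel (Human evaluation); S = 40 outputs per chatbot or 160 pooled (Blinding, randomisation and data compilation); significance level 0.05 (Statistical significance), taken as two-sided because sidedness is not stated.

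**Inputs assumed.** The split of rating variance. Let vr be the variance of rater severity and ve the residual variance of a single composite rating. Their sum is the within-output rating variance. The share vr/(vr + ve) is set at 4%, 10% and 20%.

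**Model.** Rating = output quality + rater severity + residual, with no true expertise effect. Output quality cancels within a pair.

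- True variance of the mean panel difference: 2·vr/3 + 2·ve/(3S).
- Variance that the paired t-test estimates: 2·ve/(3S) only.
- Ratio: k = 1 + S·vr/ve.
- Actual type I error ≈ 2·(1 − Φ(1.96/√k)).

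| Severity share | vr/ve | k, S = 40 | Type I error, S = 40 | k, S = 160 | Type I error, S = 160 |
|---|---|---|---|---|---|
| 0% | 0 | 1 | 5% | 1 | 5% |
| 4% | 0.0417 | 2.67 | 23% | 7.67 | 48% |
| 10% | 0.111 | 5.44 | 40% | 18.78 | 65% |
| 20% | 0.25 | 11 | 55% | 41 | 76% |

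Worked line: at 10% and S = 40, √5.44 = 2.333, 1.96/2.333 = 0.84, and 2·(1 − Φ(0.84)) = 40%. Simulation agrees to about one percentage point (for example 22% against 23% in the 4% row at S = 40).

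**On the score scale.** Assume a severity SD of 0.5 points and a residual SD of 2.0 points on the 4 to 20 scale. Chance severity differences alone give the panel gap an SD of 0.5·√(2/3) = 0.41 points. The paired t-test works with a standard error of 2·√(2/(3·40)) = 0.26 for 40 outputs, or 2·√(2/(3·160)) = 0.13 for 160. Simulation with scores rounded and limited to 4 to 20 gave type I errors of 27% and 55%. With a severity SD of 0.25 the figures were 11% and 30%; with 1.0 they were 52% and 76%.

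**Multiplicity, only if the test is run once per chatbot.** Four independent tests with no rater variance give 1 − 0.95⁴ = 18.5%. This does not add to the table, because the same six raters carry their severity into all four tests and so correlate them. At severity SD 0.5 and residual SD 2.0, simulation gave at least one significant test in 59% of runs.

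**Rater as the unit.** A t-test of three against three rater means (4 degrees of freedom) kept type I error between 4.6% and 5.5% in simulation for severity SDs from 0 to 1.5. The price is power: 80% power needs a true difference of 3.07 between-rater SDs. With 160 outputs and residual SD 2.0 this is 3.07·√(0.25 + 4/160) = 1.6 points at severity SD 0.5, and 3.07·√(1 + 4/160) = 3.1 points at severity SD 1.0.

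**The case against.** The strongest reply is that the test is valid for a narrower question. Taken literally, the sentence compares the scores of two sets of evaluators, and whether these six people's panel averages differ is something a paired t-test over outputs can answer. The article does not say that a difference will be attributed to expertise, and it admits that the evaluators are few and may not represent the wider profession. This stands in part. It does not settle the matter, because the Introduction and Human evaluation sections present the panels as levels of expertise, and a limitation stated in the discussion does not change the p-value.

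A second reply is that the contrast is peripheral. This stands in full: it is not a listed outcome, and none of the hypotheses in the discussion concerns a panel difference.

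A reader might infer that the study will, or very probably will, announce a false expertise effect. The documents do not support that. They give no severity or residual variance, and with 40 outputs the assumed shares of 4% and 10% give error rates below one half. A reader might also charge the plan with both the pooled inflation and four uncorrected tests. Only one can apply: if outputs are pooled there is a single test, and if it is run by chatbot the 40-output figures hold.

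**Conclusion.** The concern holds for inference to levels of expertise. The named test omits the between-rater variance, which for that question is the component that matters most, and more outputs worsen the error. Under assumed severity shares of 4% to 20% of within-output rating variance, the type I error is about 23% to 55% with 40 outputs and 48% to 76% with 160, against a nominal 5% that is met only if raters do not differ in severity at all. That condition is hard to assume for an unvalidated scale whose results, by the article's own account, depend on the individual evaluators.

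The conclusion rests on pairing by output, which is the only feasible reading, on severity being constant across outputs, and on the assumed shares. The rates are conditional on those shares and are not a forecast. The point is confined to a supplementary contrast: this defect leaves the primary comparison between chatbots untouched.

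**What to change.** Replace the paired t-test with a separate mixed model for this contrast, fitted to individual evaluators' ratings. Use fixed panel, chatbot and panel-by-chatbot terms, random rater nested in panel, random scenario and output, and small-sample degrees of freedom (about 4 for the panel effect). With complete ratings, the panel effect averaged over chatbots amounts to comparing three rater means with three, which is an acceptable simpler form. Report the difference with its interval. If panel differences are to be interpreted chatbot by chatbot, add a random rater-by-chatbot term so that the same omission does not recur there, and state how the four comparisons are handled.

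Otherwise, report per-rater and panel means as descriptive of these six evaluators, and give no p-value for specialists against non-specialists.

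The primary ANOVA need not change for either option, and neither needs further raters, outputs or data. The first adds one model to the plan; the second changes wording only. The cost is a wide interval and probably no significant panel difference, which is what three raters per panel can support.
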